## Abstract

**Background:**

Despite bronchiectasis being increasingly recognised as an important cause of chronic respiratory morbidity in both indigenous and non-indigenous settings globally, high quality evidence to inform management is scarce. It is assumed that antibiotics are efficacious for all bronchiectasis exacerbations, but not all practitioners agree. Inadequately treated exacerbations may risk lung function deterioration. Our study tests the hypothesis that both oral azithromycin and amoxicillin-clavulanic acid are superior to placebo at improving resolution rates of respiratory exacerbations by day 14 in children with bronchiectasis unrelated to cystic fibrosis.

**Methods:**

We are conducting a bronchiectasis exacerbation study (BEST), which is a multicentre, randomised, double-blind, double-dummy, placebo-controlled, parallel group trial, in five centres (Brisbane, Perth, Darwin, Melbourne, Auckland). In the component of BEST presented here, 189 children fulfilling inclusion criteria are randomised (allocation-concealed) to receive amoxicillin-clavulanic acid (22.5 mg/kg twice daily) with placebo-azithromycin; azithromycin (5 mg/kg daily) with placebo-amoxicillin-clavulanic acid; or placebo-azithromycin with placebo-amoxicillin-clavulanic acid for 14 days. Clinical data and a paediatric cough-specific quality of life score are obtained at baseline, at the start and resolution of exacerbations, and at day 14. In most children, blood and deep nasal swabs are also collected at the same time points. The primary outcome is the proportion of children whose exacerbations have resolved at day 14. The main secondary outcome is the paediatric cough-specific quality of life score. Other outcomes are time to next exacerbation; requirement for hospitalisation; duration of exacerbation; and spirometry data. Descriptive viral and bacteriological data from nasal samples and blood markers will also be reported.

**Discussion:**

Effective, evidence-based management of exacerbations in people with bronchiectasis is clinically important. Yet, there are few randomised controlled trials (RCTs) in the neglected area of non-cystic fibrosis bronchiectasis. Indeed, no published RCTs addressing the treatment of bronchiectasis exacerbations in children exist. Our multicentre, double-blind RCT is designed to determine if azithromycin and amoxicillin-clavulanic acid, compared with placebo, improve symptom resolution on day 14 in children with acute respiratory exacerbations. Our planned assessment of the predictors of antibiotic response, the role of antibiotic-resistant respiratory pathogens, and whether early treatment with antibiotics affects duration and time to the next exacerbation, are also all novel.

**Trial registration:**

Australia and New Zealand Clinical Trials Register (ANZCTR) number ACTRN12612000011886.

## Background

Compared to the early 20th century, the prevalence of bronchiectasis has fallen substantially. Although regarded as an ‘orphan disease’ in affluent countries, reports of prevalence of bronchiectasis are increasing [1,2]. Bronchiectasis remains a major contributor to chronic respiratory morbidity [2,3] and mortality [1,4] in both Indigenous [5] and non-Indigenous populations [6]. In our recently completed multicentre study of children newly referred for chronic cough and managed in accordance to a standardised protocol [7], 31 (9%) of the 346 children had bronchiectasis proven on radiology [8]. In the Northern Territory in Australia, the incidence of bronchiectasis in the first year of life is 118 in 100,000 [9]. The estimated prevalence of bronchiectasis is 1,470 per 100,000 in Central Australian Indigenous children aged below 15 years [10] and 1,600 per 100,000 in Alaskan Native children [11]. In the United States, reported prevalence in adults range from 4.2 to 271.8 per 100,000 [6]. However, any reported prevalence is likely to be an underestimate as many cases are misdiagnosed or coexist with other diseases like asthma [12-14] and chronic obstructive pulmonary disease (COPD) [15]. Even without accounting for these unrecognised cases, globally there are far more patients with bronchiectasis than cystic fibrosis (CF), which has a prevalence of 7.4 to 7.9 per 100,000 in the European Union and the United States [14].

Effective clinical management reduces both short- and long-term morbidity (and likely mortality) associated with bronchiectasis [16-18]. There is increasing evidence that intensive treatment of children who either have bronchiectasis or are at risk of developing severe bronchiectasis prevents poor lung function in adulthood [17-20]. Cohort data have shown that approximately 80% of newly diagnosed adults (non-smokers) with bronchiectasis reported symptoms dating back to childhood and that the duration of chronic cough (the most common symptom of bronchiectasis [21]) was related (r = −0.51, *P* < 0.001) to lung function at diagnosis [22]. Arguably, appropriate overall management and treatment of exacerbations (leading to reduction of persistent symptoms) potentially prevents or reduces deterioration of chronic respiratory disease [23].

Determinants of accelerated lung function decline in adults with bronchiectasis are the frequency of hospitalised exacerbations, increased systemic inflammatory markers and *Pseudomonas aeruginosa* infection [24]. Amongst other factors, increased mortality risk is associated with the degree of lung function impairment [25]. No prospective data exist in children. Our study and a London-based retrospective study found that, with appropriate treatment in specialised centres, lung function improves and can be maintained [18,20]. However, those with poor lung function at diagnosis, although substantially improved, were likely to still have poor lung function five years later [20]. We also found that the only significant predictor of a decline in forced expiratory volume in one second (FEV_1_) was frequency of hospitalised exacerbations [20]. Forced expiratory volume in one second (FEV_1_)% predicted decreased by 1.95% with each previous hospitalised exacerbation [20]. As airway injury in children is superimposed upon the physiological changes involving lung growth and development [26,27], improvement in childhood bronchiectasis may impact favourably upon future adult lung function. Early and effective management of bronchiectasis exacerbations in children may lead to reduced hospitalisations, better quality of life (QOL) and improved future adult lung function.

Antibiotics are one of the key interventions used to treat acute respiratory exacerbations of bronchiectasis [21,28]. However, it is biologically plausible that antibiotics are not useful for treating some respiratory exacerbations triggered by viral infections. Our retrospective study found that 34% of exacerbations were preceded by a viral-like illness [29]. While most respiratory physicians will treat exacerbations intensively (with antibiotics and airway clearance), other doctors do not. Those choosing not to use antibiotics routinely argue that most episodes of exacerbations and cough are caused by viral infections and hence do not require antibiotic therapy. This may be appropriate but viral-bacterial interactions in the airways risk prolonged endobronchial bacterial infection that, with the associated inflammatory cascade, may cause further lung injury [23,30]. Better evidence to guide the management of exacerbations in people with bronchiectasis is needed.

### Aims of the study

There are two components of BEST; here we present the study protocol of the first phase (BEST-1). The second phase of BEST (BEST-2) will address the question “Is daily azithromycin non-inferior (within 20% margin) to amoxicillin-clavulanic acid in achieving resolution of exacerbations on day 21?” The protocol for BEST-2 will be the subject of a later paper.

This first phase of our proposed national multicentre double-blind double-dummy randomised controlled trial (RCT) is designed to answer our primary questions, as follows. Amongst children with non-CF bronchiectasis, does azithromycin improve the resolution of respiratory exacerbations by day 14 compared with placebo, and does amoxicillin-clavulanic acid improve the resolution of respiratory exacerbations by day 14 compared with placebo?

Our secondary aims are to:

1. determine the effect of azithromycin or amoxicillin-clavulanic acid on the QOL, systemic inflammation, time to next respiratory exacerbation, and duration of exacerbations;

2. explore factors that predict response to antibiotics, including respiratory pathogens (viruses, bacteria, macrolide-resistant bacteria) present in respiratory secretions and blood markers; and

3. describe the point prevalence and diversity of respiratory viruses, *Mycoplasma pneumoniae* and *Chlamydia* species during exacerbations using sensitive molecular detection techniques.

Our study tests the primary hypothesis that both oral azithromycin and amoxicillin-clavulanic acid are superior to placebo in improving the resolution rate of respiratory exacerbations by day 14 in children with non-CF bronchiectasis.

## Methods/Design

### Study design

We are conducting a multicentre, parallel group, double-blind placebo RCT (with concealed allocation) to assess the impact of treatment with antibiotics (azithromycin or amoxicillin-clavulanic acid) in children with an exacerbation of bronchiectasis. Our study plan is summarised in Figure 1.

**Figure 1 F1:**
[figure not shown]
**Overall schematic study design.** Amox-clav: amoxicillin-clavulanic acid; azithro: azithromycin.

### Eligibility

The inclusion criteria are age below 18 years at time of study enrolment; diagnosed with bronchiectasis by a respiratory physician following high resolution computed tomography in the five years immediately prior to study entry or, if diagnosed earlier, have been followed regularly by a respiratory physician for treatment of bronchiectasis; and has experienced two or more respiratory exacerbations in the 18 months prior to study entry.

Exclusion criteria are current severe exacerbation of bronchiectasis (dyspnoea, hypoxia or hospitalisation), recent (in last 8 weeks) in the entry; CF; liver dysfunction; allergy or sensitivity to penicillin or macrolides; current or recent lower airway infection by a member of the Pseudomonas genus group of Gram-negative bacteria (in the four months prior to study enrolment); has received antibiotics belonging to the macrolide or penicillin class of antibiotics within three weeks immediately prior to study entry; or is currently receiving oncological treatment.

### Recruitment

Eligible children will be identified from clinics in our centres (Brisbane, Perth, Darwin and Melbourne in Australia and Auckland in New Zealand). Parents will be approached and informed consent obtained. Baseline pre-exacerbation data will be collected (Figure 1), parents contacted monthly and children reviewed every three months. Parents will be educated specifically on symptoms of exacerbations and asked to contact the research nurse at the onset of an exacerbation.

### Intervention and follow-up

A double-dummy design is planned. If eligibility is fulfilled and after informed consent has been obtained, the child is randomised to one of three arms. At the start of the exacerbation, the child will receive amoxicillin-clavulanic acid with placebo-azithromycin, azithromycin with placebo-amoxicillin-clavulanic acid or placebo-azithromycin with placebo-amoxicillin-clavulanic acid. Amoxicillin-clavulanic acid dose is 22.5 mg/kg/dose (up to 40 kg) twice a day (max 900 mg/dose). Azithromycin dose is 5 mg/kg/day, max of 200 mg daily. Equivalent volumes in placebo will be given in all arms. All treatments will continue for 14 days.

An exacerbation is defined as an increase in sputum volume or purulence, or three or more days of change in cough (> 20% increase in cough score [31] or type (dry to wet) [32]). We validated this definition in our prospective study and found that the kappa values (between clinicians) of these symptoms and signs were excellent (> 0.75) [33]. Daily diaries will also be collected during exacerbations until the scores for two or more days reflect the child’s ‘baseline’ state, which for each child will be established at enrolment, prior to any exacerbations. This assessment consists of a combination of symptoms (daily cough (yes/no), cough quality (wet/dry/none) and cough score [31] averaged over two consecutive days) and signs (sputum colour (if any present) using a colour chart card (BronkoTest Ltd, London, UK), crackles on chest auscultation). Children will be reviewed on days 7 and 14 and at resolution of the exacerbation. The exacerbation is considered ‘resolved’ when symptoms and signs are the same as ‘baseline’ state. Post exacerbation, the children will be followed-up and clinically evaluated every three months for 18 months or until their next exacerbation. ‘Time to next exacerbation’ will be determined by the number of days from ‘resolution of current exacerbation’ to beginning of the next exacerbation.

### Randomisation, allocation and blinding

Upon enrolment, the child is assigned to the next unique number on the appropriate stratified list. The allocation will be performed by the trial pharmacist at the Royal Children’s Hospital in Brisbane. Randomisation is stratified by site (Brisbane, Perth, Darwin, Melbourne, Auckland), age (≤ 5 or > 5 years) and underlying aetiology (idiopathic/post-pneumonia or all other causes). The randomisation sequence was computer generated and used permuted blocks. The allocation sequence is concealed at all times throughout the study. The computer generated allocation sequence was prepared by a statistician external to the study team.

The placebo medications, specifically manufactured by the Institute of Drug Technology Australia Limited (Melbourne, Victoria), have a similar taste and colour to their respective antibiotics. Both active medications (amoxicillin-clavulanic acid and azithromycin) are repackaged by the Institute of Drug Technology. Thus both the amoxicillin-clavulanic acid and azithromycin and their respective placebos are in identical opaque bottles. For both types of trial medications, equal volumes of water are added using a syringe and needle by punching the seal. Adherence will be assessed by parent report and return of empty bottles.

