### Sample size

We plan to enrol 189 children (63 per arm), providing 84% power (α = 0.0245, two-sided) to detect a halving of the number of children in the active arm achieving resolution by day 14 (that is, azithromycin or amoxicillin-clavulanic acid: 60% resolved by day 14, compared with placebo: 30% resolved). This is a conservative estimate when compared with our prospective data of persistent symptoms in 24% of children based on the same diary card [50]. As the primary outcome will be obtained in all enrolled children, a drop-out has not been factored in for the intention-to-treat analysis. With 20% drop-out rate, data from 153 children (51 per arm) for ‘per protocol’ analysis provides a study power of 75%. Both treatment arms are compared with the same placebo arm. While the maximum efficiency is attained by allocating more children to the placebo arm (that is, using an allocation ratio of 1:1:√2), we chose to use a 1:1:1 allocation due to ethical concerns of deviating from standard care in respiratory centres.

In the main secondary outcome (PC-QOL), based on a between-group difference of 0.9 (minimum important difference [42]) (SD 0.9), our sample size provides power of 100% (α = 0.05) for data from at least 147 children (that is, assuming at least 80% retention of the 189 children enrolled). For secondary aim 2 (exploring factors that predict response to antibiotics), we will be examining eight main factors and thus a sample size of 147 exceeds the recommended minimum (n = 10 per factor) [51]. The eight factors are smoking, age, underlying aetiology, detection of virus (any versus none, then single versus multiple viruses), presence of azithromycin resistance and blood markers (IL-6, IL-10, IP-10 levels).

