## Trial status

We commenced recruitment in Darwin in mid-March 2012, Brisbane in June 2012 and the other sites are expected to commence in August 2012. We commenced randomisation in late May 2012.

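### The protocol contradicts itself on when children are randomised and on what 189 counts, so its reason for making no intention-to-treat allowance holds only if *enrolled* means *randomised at exacerbation onset*

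*Protocol article*

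**What the plan says.** The Protocol article describes two stages. Children are identified in clinic, consent is obtained and a waiting phase follows: "Baseline pre-exacerbation data will be collected (Figure 1), parents contacted monthly and children reviewed every three months" (Recruitment). The baseline state against which resolution is judged is one "which for each child will be established at enrolment, prior to any exacerbations" (Intervention and follow-up). Medicine comes later: "At the start of the exacerbation, the child will receive amoxicillin-clavulanic acid with placebo-azithromycin", with the same timing for the other two arms.

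On allocation, two sections agree. Randomisation, allocation and blinding says "Upon enrolment, the child is assigned to the next unique number on the appropriate stratified list". Intervention and follow-up says "If eligibility is fulfilled and after informed consent has been obtained, the child is randomised to one of three arms". Neither makes an exacerbation a condition.

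Other sections do not fit this:

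- Trial status gives mid-March 2012 for recruitment at the first site and June 2012 for the second, then adds "We commenced randomisation in late May 2012".
- The Methods paragraph of the Abstract has 189 children randomised. Sample size has 189 enrolled.
- Sample size says "As the primary outcome will be obtained in all enrolled children, a drop-out has not been factored in for the intention-to-treat analysis".

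Statistical analysis and reporting analyses children by the arm allocated.

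**The concern.** The primary outcome is resolution of an exacerbation by day 14. It does not exist for a child who has had no study exacerbation. If the list number is taken at enrolment and analysis is by allocation, such a child belongs to the intention-to-treat set without an outcome. The non-resolved rules in Primary outcome and in Statistical analysis and reporting cover withdrawal, additional antibiotics, clinical worsening and drop-out. They do not cover a child still waiting.

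The 63 per arm, the 84% power and the absence of any allowance all rest on the completeness sentence. Whether that sentence is true depends on a date that the document gives in two incompatible ways. A reader cannot tell who is in the primary analysis, or whether 189 is a count at the clinic door or at the start of treatment.

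**Working it through.** **1. The passages side by side.** If children are allocated on enrolment, the first recruit is randomised on entry, so recruitment and randomisation begin together. Trial status has recruitment from mid-March and randomisation from late May. The second site opened only in June, so the gap arose while only the first site was recruiting. That fits randomisation at a later exacerbation, but does not prove it.

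**2. The stated power.** Inputs from Sample size: 60% v 30% resolved, n = 63 per arm, two-sided α = 0.0245 (z = 2.249). Continuity-corrected two-proportion power:

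Φ{ [ |p₁ − p₂| − 1/n − z·√(2p̄(1 − p̄)/n) ] / √( [p₁(1 − p₁) + p₂(1 − p₂)]/n ) }

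- Numerator: 0.300 − 0.0159 − 2.249 × √(0.495/63) = 0.2841 − 0.1994 = 0.0848
- Denominator: √(0.45/63) = 0.0845
- Φ(1.003) = 84.2%

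Fisher's exact test gives 84.5%. The stated 84% is reproduced, so the arithmetic is sound and only the premise is in question.

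**3. How long the wait could be.** The document gives no waiting time or maximum. Its rationale section reports 156 exacerbations in 900 child-months, a rate of 0.173 per month: mean wait 900/156 = 5.8 months, median ln 2/0.173 = 4.0 months. With a constant common rate, P(none by T) = exp(−rate × T). The minimum history in Eligibility, two in 18 months, is a rate of 0.111.

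| Months waited | No exacerbation at 156/900 | No exacerbation at 2/18 |
|---|---|---|
| 6 | 35% | 51% |
| 12 | 12.5% | 26% |
| 18 | 4.4% | 14% |

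If rates vary between children, the shares at the cohort rate rise. With gamma variation of shape 2 or 1 they are 24% or 32% at 12 months and 15% or 24% at 18 months.

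**4. Power if allocation is at enrolment.** Let f be the fraction of allocated children with no treated exacerbation; f is an assumption. Left out: n = 63(1 − f), rates unchanged. Scored as non-resolved: n = 63, rates 0.60(1 − f) v 0.30(1 − f). Enrolment needed to keep 189 with a treated exacerbation: 189/(1 − f).

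| f | Left out: n per arm, power | Scored non-resolved: rates, power | Enrol |
|---|---|---|---|
| 0 | 63, 84.2% | 60 v 30, 84.2% | 189 |
| 5% | 60, 81.9% | 57 v 28.5, 79.9% | 199 |
| 10% | 57, 79.4% | 54 v 27, 75.3% | 210 |
| 20% | 50, 72.3% | 48 v 24, 64.9% | 237 |
| 30% | 44, 64.9% | 42 v 21, 53.9% | 270 |

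**5. Power if randomisation is at onset.** Then f = 0 among randomised children. Withdrawals and drop-outs are scored as non-resolved, so every randomised child has an outcome and 84% stands for 189 randomised.

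**The case against.** The strongest reply is that this is loose wording and that children are in fact randomised at onset. Trial status and the Abstract point that way. Excluding a current severe exacerbation makes most sense if eligibility is judged when the child presents with one. Figure 1, the study schematic, is not available here and may settle the matter. Much of this stands, and allocation at enrolment should not be taken as the established design.

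A reader might go further and infer that never-treated children do enter the intention-to-treat set, are counted as failures and dilute both comparisons. The documents do not support that. The timing is contradicted, and no rule scores a waiting child as non-resolved; only one who dropped out while waiting would be. The lower power column is therefore conditional twice over.

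Nor is there bias between arms from this source. Under blinding, whether a child has an exacerbation before any study drug is independent of arm, so leaving such children out costs numbers, not validity.

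A reader might also object that the antibiotic exclusion applies "within three weeks immediately prior to study entry" and could be out of date when treatment starts. That is a side point: an article commonly leaves re-screening to the full protocol.

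The reply does not rescue the text. Two operative sections place allocation before the exacerbation, and the completeness sentence speaks of enrolled children in a design where enrolment comes first.

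**Conclusion.** The concern holds as an internal contradiction with a dependent false premise. The document does not say consistently when randomisation occurs or what 189 counts, and its reason for making no allowance is untrue unless *enrolled* is read as *randomised at exacerbation onset*.

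The size depends on which reading is real. With randomisation at onset, nothing is lost and the repair is wording. With allocation at enrolment, power for each primary comparison falls from 84% to about 79% (left out) or 75% (scored non-resolved) at f = 10%, and to 72% or 65% at f = 20%. These figures assume the planned 60% v 30%, a continuity-corrected test and an f that the document does not give. That the wait commonly lasts months is inferred from the authors' cohort rate, not stated.

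**What to change.** Reconcile the Abstract, Intervention and follow-up, Randomisation, Sample size and Trial status as follows:

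- State that the next number on the stratified list is taken when the child presents with the qualifying exacerbation, immediately before trial medicine is issued.
- Define 189 (63 per arm) and the intention-to-treat set as all children so randomised.
- In the completeness sentence, change enrolled children to randomised children. The 84% then stands.
- Say which date study entry means, so that the eligibility windows have a fixed anchor.

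If allocation really is at enrolment and cannot be moved, define the primary set as allocated children who start a study exacerbation, state the expected f, and either restate the power or raise enrolment to 189/(1 − f).

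Cost: if onset is already the practice, only wording changes. If not, the change is operational. One pharmacist in Brisbane allocates for five centres in two countries and would release numbers at onset instead of at consent, and Specimen collection notes that some children cannot attend at onset. Some enrolled children will never be randomised, so recruitment must exceed 189.
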